#### Aim 3, retention

To determine whether retention in care is higher among people in intervention compared to control communities, including (a) proportion of ART initiated patients not defaulting from care (with no more than a 90-day gap in treatment during 12 months) and b) those ineligible for ART returning for CD4 staging at 6-month intervals.

#### Aim 4, mechanisms

To explore changes in community mobilization domains as well as how differences in each domain associate with changes in study outcomes (testing, linkage, and retention) over time.

### Community randomization

Communities involved previously in community mobilizing activities (*n* = 12), those not yet fully enumerated in 2014 (*n* = 3), and with fewer than 500 permanent residents (*n* = 1) were not eligible to participate, leaving 15 communities to randomize. In order to achieve a balance among villages on the key covariates at baseline, a restricted or balanced randomization approach [54] was used, taking into account population size, distance to closest health facility, average levels of SES based on household assets [55], temporary migration, female-headed households, and baseline community mobilization scores [53], collected as part of a survey in 2014. Cluster allocation cannot be concealed as CM events and activities are held in public spaces. Further, village leaders were consulted about the trial, consented for their villages to participate, and were present for the allocation. A randomization event was carried out with community representatives. A biostatistician unfamiliar with the area and the villages generated 50 different grouped combinations of intervention and control villages, and these combinations were printed on strips. The assignment was revealed by asking a community volunteer to pick the winning randomization scheme out of a bucket containing all 50 possibilities. The program was then launched in the presence of local leaders and community members.

### Intervention design

Overall, our mobilization model adheres to the theory that social barriers necessitate social change solutions—those which move beyond merely providing services or empowering individuals to use services and that instead construct a collective response out of a group of individuals [28]. As a result, our intervention addresses social barriers to testing, and linkage to and retention in HIV care, specifically, poor awareness or understanding of HIV care; fear and stigma associated with HIV infection, clinic attendance, and disclosure; lack of social support; and gender norms, particularly those that deter men from accessing care. These content areas are addressed by implementing activities across the intervention villages that engage communities in social change—specifically activities that map onto six CM domains distilled from the social sciences literature and validated in the study area (see Fig. 2) [52]. The six domains of mobilization that are being addressed for CM to successfully impact HIV prevention are (1) a shared issue or concern that is the target of change, (2) community sensitization or building of critical consciousness, (3) an organizational structure with links to groups/networks, (4) leadership (individual and/or institutional), (5) collective activities/actions, and (6) community cohesion. These domains represent community factors integral to social change that must be addressed or modified for mobilization to occur and to impact behaviors, social norms, and health outcomes in the communities.

**Fig. 2 Fig2:**
[figure not shown]
Conceptual framework of the intervention, community mobilization components, and study goals

The program is being carried out in partnership with Sonke Gender Justice, a South African non-governmental organization (NGO) dedicated to activism and health programming at the intersection of HIV and gender equity. Intervention activities and workshop content have been adapted from material that has been compiled, pilot tested, and successfully utilized in our previous collaborative work on community mobilization to address gender norms [56]. In preparation for the intervention we both refined previously designed activities to fit the new programmatic content and further developed new activities addressing social barriers to testing, linkage to, and retention in care. New activities, workshop content, print materials, and short films were developed to specifically address the issue of treatment as prevention (TasP) and HIV treatment literacy. We also added more in depth content on stigma and social norms surrounding HIV and health care utilization. Over 16 community-based activities have been developed, standardized and manualized into a toolkit of community mobilizing activities; 50 modules covering 7 themes have been included in a workshop manual; and a handbook for creation of community mobilizing teams has been developed and refined [57]. The mobilizing team named the intervention “Tsima ra rihanyu,” which means “working together to plow the fields for health” in the local language.

Tsima ra rihanyu is being implemented over 3 years by a team of 16 community mobilizers with two intervention coordinators, a logistician, and a member of the senior staff at Sonke Gender Justice. Mobilizers were selected from intervention communities and assigned to work in their own villages whenever possible. These individuals underwent extensive training from master trainers at Sonke on all intervention activities and are supervised by the intervention coordinators. As part of the Tsima ra rihanyu activities, the mobilizers also identified and trained community action teams (CATs) in each village. CATs are volunteers from the community who engage with the CM activities and lead mobilization efforts in their community; mobilizers work closely with CATs as they implement activities. This CAT model has been successfully utilized by Sonke in previous efforts.

Intervention activities aim to open dialogue and community discussion about testing, linkage to and retention in care through CM activities, harnessing networks for message dissemination, and forging organized community action through establishing CATs, engaging leadership, and fostering community cohesion to support people living with HIV (see Table 1). The CM team, along with the CATs, are carrying out activities to generate *a shared concern and raise consciousness* around engagement in HIV prevention and care, with a focus on the importance of testing, linkage to and retention in care for individuals, and overall community health. Activities to *raise consciousness* include intensive small group workshops, community outreach, including theater, debates and discussions, and digital story workshops—an event where real stories of individuals’ experiences with testing and engagement in care are told and then screened to generate discussion, and engagement with clinic staff. We launched the intervention with smaller group activities and workshops that focus on raising community consciousness and generating a shared concern around testing, linkage to care and treatment, and identifying CAT membership in order to set the stage for implementation of the full complement of CM activities. CATs act as community/clinic liaisons and work with the CM team to *engage local leadership* and stakeholders in these discussions and also work with existing *organizations and networks*, such as support groups or home-based care groups, as part of efforts to build community consciousness and shared concerns around TasP. As a next step, the CATs and mobilizers work to *lead collective actions* around testing, linkage, and retention such as designing community murals, hosting soccer tournaments, and other appropriate community events. In these events, efforts to build social cohesion and engage leadership are emphasized. Illustrative activities are included in Table 1.

**Table 1 Tab1:** Intervention activities addressing social barriers to treatment as prevention, mapped onto community mobilization domains

	Social barriers to TasP			
CM domains	Stigma related to testing, care, and treatment	Increased knowledge (diminish fears) about testing and treatment	Gender norms around testing and treatment	Social support around testing and treatment
Building shared concerns and community consciousness	*2-Day intensive and single session workshops -focus on community stigma around testing/treatment *Door to door outreach *Digital stories and film screening *Engaging with clinic staff	*Street theater-focused on barriers to testing/treatment *Digital stories and films on testing and care experiences *Door to door outreach *Educational events	*2-Day and intensive and single session workshops on gender norms and the benefits/barriers to men engaging in testing and care *Street theater addressing gender norms	*2-Day intensive and single session group workshops-focused on community barriers to testing and treatment *Door to door outreach *Digital stories screening
Engaging leadership and stakeholders (includes traditional leaders, religious leaders, clinic leaders, other community stakeholders)	*Engaging leaders around importance of TasP and barriers in community *Intensive workshops with leaders on HIV stigma, testing/treatment *Pursuing leadership commitments to achieving village testing and treatment targets (goal setting)	*Engaging leaders around importance of TasP and barriers in community *Monthly 1-day small group workshops focused on benefits of testing and treatment in community	*Engaging leaders around the importance of men engaging in health care *Seek support from leadership to enter places of work, taverns, places where men congregate	*Identifying home based care support groups in CAT development *Engaging leaders in creating support networks for testing and treatment as a community benefit *Goal setting with leadership
Orgs/networks (includes NGOs, CBOs, CATs, other family or community groups/networks)	*Working with the key groups to openly support and include testing and treatment in their work in the communities	*Working with key groups to understand how testing and care can improve community well-being *Message dissemination through networks.	*Working with the key groups (employers, small businesses, sport teams, etc..) to support engagement of men in testing/care *Dialogues with church leaders addressing support for male testing/care	*Identifying home-based care groups and PLWH in CAT development *Partnering with support and treatment networks *Founding community support groups
Collective action	*Murals that address stigma related to testing and treatment *Events to support testing campaigns/treatment access *Encouraging Tsima members and affiliates to HIV test together	*Soccer tournaments that highlight importance of testing and treatment *Events to support testing campaigns/treatment access *Home education (open house) events for networks/groups	*Community events/forums that address gender norms and accessing HIV care *Murals that address gender norms and HIV care	*Community events conducted by CATS, PLWH, and home-based care groups to increase community support around TaSP *Encouraging Tsima members and affiliates to HIV test together
Social cohesion	*Visible community support (events/forums) to reduce stigma–working with PLWH *Community events to dialogue around how stigma affects the community and how communities can respond	*Identifying home based care groups and PLWH in CAT development–providing safe space for discussion and support *Events to support stronger care and treatment networks	*Dialogues with men’s groups or associations–addressing male support for testing/care. *Building CATs with men, including men LWH	*Work with home-based care and CATS to establish PLWH support networks *Extend networks and activities to families *Join CATs, local leaders, and clinic staff in testing and treatment strategies.

### Intervention monitoring

Intervention activities are continuously monitored in order to quantify intervention consistency (fidelity) as well as dosage and reach by village. Data collection forms are completed by mobilizers and CAT members in order to capture which activities are undertaken in the communities and how many residents were in attendance. Monitoring reports are generated monthly and quarterly to assess the estimated proportion of residents exposed to the CM intervention in each village and to ensure the team is reaching intervention coverage targets. With this system capturing data in real time, any indication that a village may fall below a given threshold (i.e., reach 25% of the village population with workshops annually) can be noted early and corrective action taken to ensure the village receives additional support from the mobilizing team. In our past experience implementing CM, this system has allowed us to ensure that all activity targets are met within the specified timelines.

### Data collection

Continuous data collection of HIV-testing and care delivery visits is underway at all ten health facilities in the study area by a team of trained data capturers stationed at the facilities, who both obtain written informed consent from patients to capture clinical visit data and conduct the HDSS-health facility data linkage in real time (Fig. 3). The data linkage is done using deterministic and probabilistic approaches. After obtaining written informed consent from a new patient, the data entry clerk collects a set of identifiers that are used to search the Agincourt HDSS data. Linkage is attempted using national ID number and, if a match is not found, then a second attempt is performed using a combination of mobile phone number, first name, and date of birth. If a match is still not found, a search is done using an algorithm based on the Fellegi-Sunter probabilistic record linkage model [58]. The key identifiers include name, surname, age or date of birth, sex, village of residence, and name of another person living in the household [59]. When potential matches are found, they are reviewed in the presence of the patient to confirm his or her identity. In addition to identification of the patient in the population database, the data entry clerk extracts clinical information from the patient’s file and logs all follow-up visits, entering clinical information directly into a laptop hosting the linkage system. The linkage system encrypts all data as soon as it is entered; identifying information (e.g., name and phone numbers) are excluded from analytic datasets.

**Fig. 3 Fig3:**
[figure not shown]
Study design and data collection components

To measure coverage of the intervention and changes in the CM domains and other key variables in each community over time, a cross-sectional, population-based survey was administered prior to the intervention and a second survey will take place following the intervention (Fig. 3). The surveys aim to capture 1200 randomly sampled adults, aged 18–49 years, from the HDSS population with approximately 75 people sampled in each of the 15 study villages at both time points. Eligibility criteria for participation in community surveys include residence in the home (spending a majority of nights at home), being 18–49 years of age, and having lived in the study area for at least 9 of the past 12 months. Surveys are interviewer-administered in the participant’s home using computer assisted personal interview (CAPI). Only one individual per household can be selected. Fieldworkers visit the selected homes to confirm eligibility and explain the study. Written informed consent is obtained from all participants prior to the survey; both consent and the survey are offered in the local language, Shangaan, or English. All procedures were approved by the Institutional Review Boards at the University of North Carolina-Chapel Hill and the University of California-San Francisco, the Human Research Ethics Committee (Medical) at the University of the Witwatersrand in South Africa, and the Mpumalanga Department of Health and Social Development Research Committee.

### Study measures

#### Primary exposure

Residence in an intervention or control community is the primary predictor variable for all analyses. Community of residence will be determined using the HDSS data. Household and vital events data are updated annually and include births, in- and out-migrations and deaths. Although few individuals are expected to move within the study area over the course of the study, for those who do move, exposure will be determined dynamically over the course of the study such that individuals will be considered exposed if they were resident in an intervention community in the time period immediately prior to the outcome. Table 2 summarizes the quantitative data elements that include exposures, outcomes, mediators, and social and demographic co-variates.

**Table 2 Tab2:** Summary of quantitative data elements

Domain	Instrument/measure	Data source and frequency
Primary exposure		
Village	Village of residence (binary; intervention vs. control village)	HDSS-annual
Primary outcomes		
Testing uptake (aim 1)	Binary: tested/untested past 12 months, among HIV-negative or unknown status residents	Electronic health facility records-ongoing
	Binary: known HIV status–either confirmed positive or tested within the last 12 months	Electronic health facility records-ongoing
Linkage to HIV care (aim 2)	Binary: received baseline CD4 results and evidence of follow-up care (additional CD4, viral load, or treatment initiation) within 3 months of testing HIV positive	Electronic health facility records-ongoing
	Binary: treatment initiation within 3 months of positive diagnosis among those eligible for ART	Electronic health facility records-ongoing
Retention in HIV care (aim 3)	Binary: HIV patients on or initiating ART who have no more than a 90-day gap in medication received in the 12-month period (no defaulting).	Electronic health facility records-ongoing
	Binary: HIV patients not ART eligible^a^ who have a repeat CD4 test 6–12 months after initial CD4	Electronic health facility records-ongoing
Meditator/mechanism		
Community mobilization	Six domains of community mobilization measure [53]	Population-based surveys (years 1 and 5)
Covariates		
Demographics	Age, SES, gender, migration status	HDSS-annual
Social norms	Stigma [81]; gender norms [41]; community support for HIV testing and treatment [53]	Population-based surveys (years 1 and 5)
Secondary outcomes		
Testing (aim 1)	Median CD4 of people initiating ART (to explore earlier testing, entry into care)	Electronic health facility records-ongoing
Re-engagement in care (aims 2 and 3)	Patients out of care (not retained) who are re-engaged in care (have a CD4 test/initiate or re-initiate treatment).	Electronic health facility records-ongoing
Viral suppression	Proportion of residents with viral load <400 copies/ml	Electronic health facility records-ongoing
Secondary exposure		
Intervention coverage	Reported exposure to intervention events	Population-based surveys (years 1 and 5)

^a^Prior to September 2016, patients were considered ART eligible with one or more of the following criteria: pregnancy, CD4 count lower than 500 cells/mm [3], active tuberculosis, WHO stage 3 or 4, or initiation of ART per clinician discretion. Universal treatment was planned to be instituted in September 2016; therefore, all HIV-positive individuals will be considered treatment eligible after this date; the pre-ART definition will only apply to the period prior to implementation of the universal treatment guidelines

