### Specific aims

The CM intervention is being evaluated by comparing uptake of testing, linkage, and retention in care in 15 communities randomized to either an intervention condition (*n* = 8) or a control condition (*n* = 7) located within the Agincourt HDSS. To measure outcomes in each village, we are linking the longitudinal population-based HDSS data to a health facility-based electronic clinical tracking system used in all HDSS health facilities. The linkage of the health facility and census data allows us to establish an open cohort of approximately 34,000 18–49-year-old residents that includes exposure data (village of residence) as well as outcome data (HIV-related clinical care). Using these data, we will evaluate the effects of the CM intervention by village randomization arm as well as characterize the HIV care cascade in a high prevalence population. We will also evaluate the conceptual model, including the hypothesized CM processes [52], through community surveys to monitor intervention exposure and community level change using validated CM measures [53]. The specific aims of the study include:

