#### Primary outcomes

For each aim, the primary source of data for outcomes is the electronic health facility data linked to the HDSS. An electronic record will be created for every resident of the 15 study villages captured in the population database; with this approach, we will treat the entire eligible (18–49-year old) population in the area as an open cohort, assuming no clinic visits were made if none were captured for a given individual. Study outcomes include HIV testing uptake in the past 12 months among residents of negative or unknown status (aim 1); linkage to HIV care, or having returned to the clinic following diagnosis for ART initiation or follow-up care (aim 2); and retention in care, defined as remaining on ART with no more than a 90-day gap in coverage over a 12-month period (aim 3).

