### Power

Minimum detectable differences were calculated according to the methods for proportions in cluster randomized trials proposed by Hayes and Moulton [54], yielding conservative effect size estimates based on clustering by villages. Based on the HDSS data, there are approximately 30,000 adults 18–49 in the study area. We assumed an HIV prevalence of 33% in the adult target population (18–49-year old) [51]. If we conservatively estimate that testing is constant at 35% of the population, at least a third of those tested each year were not tested previously in the study period, and that test positivity is 15% (again a conservative estimate), 449 cases of HIV would be newly identified each year. We further assumed that approximately 50% of individuals who present for CD4 staging would be eligible for HIV treatment under 2014 guidelines. Approximately 6000 individuals were known to be on treatment at clinics in this area in 2014. Our survey data from 2012 suggests that HIV testing in this region exhibits an intra-class correlation of 0.014. In adjustments of power calculations for clustering of outcomes by village, we conservatively assumed an intra-class correlation of 0.05. Table 3 includes outcome estimates for the control proportions based on current literature [18, 26, 27, 68, 79], and the target (intervention) proportions with the minimum increase in proportions that would be detectable as a statistically significant change at alpha of 0.05 and power of 0.80, given the above assumptions. In 2016 (1 year into data collection), the South African government announced universal HIV treatment. This should increase our sample size to assess initiating ART (aim 2) and retention in care (aim 3) in the second and third years of the study.

**Table 3 Tab3:** Power calculations–minimum detectable effects

Outcomes: proportion of population	Current estimate	Intervention group target	Minimum detectable difference (proportion)
Testing; tested in past 12 months	35%	60%	19%
Linkage; undergoing CD4 staging within 3 months of positive test	65%	85%	18%
Linkage; eligible for ART who initiate treatment within 3 months	60%	80%	19%
Retention; HIV positive who remain in care at 12 months	50%	70%	19%

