## Trial status

The first cross-sectional survey was conducted between August-November, 2014. Data collection at health facilities in the study catchment area was rolled out across nine clinics between June and August 2015 and in an additional clinic from July 2016; clinic data capture is scheduled to continue in all clinics through 2018. Intervention activities commenced on 1st August 2015; the intervention is currently entering the second year of a 3-year intervention, scheduled to close out in July 2018.

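### Table 2's ART-retention rule passes a permanent stop that begins in the last 90 days of the 12 months, a patient whom the text and Table 3 would not count as still in care, and it sets no minimum time on ART

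*Protocol article*

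**What the plan says.** The protocol article describes ART retention, a primary outcome under aim 3, in four places.

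- **Specific aims, Aim 3:** "proportion of ART initiated patients not defaulting from care (with no more than a 90-day gap in treatment during 12 months".
- **Study measures, Table 2:** "Binary: HIV patients on or initiating ART who have no more than a 90-day gap in medication received in the 12-month period (no defaulting".
- **Primary outcomes:** "remaining on ART with no more than a 90-day gap in coverage over a 12-month period".
- **Power, Table 3:** "Retention; HIV positive who remain in care at 12 months", with 50% in the control arm, a 70% target and a minimum detectable difference of 19 points.

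The population changes from ART-initiated patients, to patients on or initiating ART, to HIV-positive people. The clock changes from treatment, to medication received, to coverage. Two of the four (Primary outcomes and Table 3) contain a status at the end of the period. The other two contain only a gap rule.

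No place says whether the 12 months run from each patient's ART start or form a fixed window, or whether records after the period count towards a gap. Trial status reports that "clinic data capture is scheduled to continue in all clinics through 2018", with the intervention closing in July 2018.

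**The concern.** A rule that looks for a gap longer than 90 days inside a 365-day period has a blind spot at the end. A patient who last receives medication on day 280 and never returns shows an 85-day gap by day 365 and passes Table 2. That patient is not in care at 12 months in the sense of Table 3, and it is hard to describe the patient as remaining on ART. This holds whether the 12 months are a calendar window or the patient's own.

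The second issue depends on the reading. Table 2 pools established patients with those initiating ART and asks for no minimum time on treatment. If the period is a fixed window, a patient starting in its last 90 days cannot accumulate a failing gap. The intervention aims to raise testing and ART initiation, so the arms may differ in their share of recent starters and would then not be scored on equal time at risk.

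At stake is the size of the difference that a primary comparison can show, and whether the outcome analysed is the one the trial was sized on.

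**Working it through.** **1. The plan's own figure.** Table 3 gives 19 points for retention. Inputs from the Power section: p0 = 0.50, "at alpha of 0.05 and power of 0.80" (two-sided assumed), and "we conservatively assumed an intra-class correlation of 0.05". Patients per village are not stated; I assume 6000/15 = 400. The clusters are "15 communities randomized to either an intervention condition" (8) or control (7). I solved d = (1.960 + 0.842) × √(V/c) for c from 7.5 (the average per arm) down to 6 (a small-sample correction).

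- Intra-class correlation form, V = [p0(1−p0) + p1(1−p1)] × [1 + 399 × 0.05]/400: d = 16.1 to 17.9 points.
- Coefficient-of-variation form, V = [p0(1−p0) + p1(1−p1)]/400 + k²(p0² + p1²), with k² = 0.05 × (1−p0)/p0: d = 20.0 to 22.9 points.

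The stated 19 lies between the two. It can be neither confirmed nor called wrong, and the point does not rest on it.

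**2. The blind spot.** 365 − 90 = 275. A stop beginning after about day 275 cannot produce a gap of more than 90 days by day 365. That is 90/365 = 24.7% of the year.

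**3. Size for patients on ART at the start of the period.** Assume a constant stopping hazard and no return to care. With true 12-month retention R, the hazard per year is h = −ln R, and the scored proportion is exp(−h × 275/365).

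- R = 0.50: h = 0.693; exp(−0.522) = 59.3%.
- R = 0.70: h = 0.357; exp(−0.269) = 76.4%.

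The true difference of 20 points is scored as 76.4 − 59.3 = 17.1. The 19 in Table 3 was set at a control value of 50%. Moving p0 to 59.3% in the formulas of step 1 lowers the detectable difference by 0.8 to 1.4 points, so 19 becomes about 17.6 to 18.2, still above 17.1.

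**4. New starters, calendar-window reading only.** With starts uniform over the window, the scored proportion is 90/365 + [1 − exp(−h × 275/365)]/h.

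- R = 0.50: 0.247 + 0.407/0.693 = 83.3%.
- R = 0.70: 0.247 + 0.236/0.357 = 90.7%.

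At the same hazard, starters therefore score 24.0 points (R = 0.50) or 14.3 points (R = 0.70) above established patients.

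**5. False difference from mix.** The Power section gives about 6000 people on treatment and 449 new diagnoses a year. If all 449 start ART, starters are 449/6449 = 7.0% of the denominator, and automatic passes are 7.0% × 24.7% = 1.7%. Suppose starters rise in one arm only:

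- in proportion to the testing target (60/35): 770/6770 = 11.4%, a shift of 4.4 points; 0.044 × 24.0 = 1.1 points;
- doubled: 898/6898 = 13.0%, a shift of 6.1 points; 0.061 × 24.0 = 1.5 points.

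At R = 0.70 these become 0.6 and 0.9 points.

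**6. Overstatement against being on ART at day 365** (percentage points):

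| True R | On ART at day 0 | New starters, calendar window |
|---|---|---|
| 50% | 9.3 | 11.2 |
| 70% | 6.4 | 6.6 |
| 80% | 4.5 | 4.4 |
| 90% | 2.4 | 2.2 |

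**The case against.** The strongest reply is that this is an abridged article. The window start and the handling of a gap still open at the end are normally fixed in the full protocol or analysis plan, and nothing says later records will be ignored. The Primary outcomes text also adds the words about remaining on ART, which would probably fail the day-280 patient. This stands in part: silence on the window start is not itself an error. What remains is that the stated definitions do not agree. Table 2 tests a gap only, while the text and Table 3 describe a status that the gap rule does not test.

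A reader might infer four stronger claims. The article does not support them.

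- **That no default in the last 90 days can be detected.** A gap that began earlier and passes 90 days within that stretch is detected. Only gaps that begin there are missed.
- **That late starters always pass.** This needs a calendar window. Repeated post-baseline measurements in the GEE analysis fit that reading but do not fix it. Aim 3 refers to ART-initiated patients, and other outcomes in Table 2 run from a patient event. If the 12 months run from ART start, the blind spot is the same for new and established patients.
- **That new starters are the most inflated.** Against status at day 365 the two groups differ by about 2 points or less, and the order reverses at true retention of 80% and above (step 6). The large gap appears only when part-year exposure is set against a full 12 months.
- **That retention is overstated on balance, in favour of the intervention.** Visits not captured are treated as not made (Primary outcomes), and movers still in care may be classed as lost (Discussion). Both push retention down. In step 3 the rule dilutes a true effect; only the mix mechanism can create a false one.

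The planned tracing of 10% of those classified as lost does not repair the rule, because a patient scored as retained would not ordinarily be in that sample.

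**Conclusion.** The point holds in limited form. As worded, Table 2 counts as retained a patient whose permanent stop begins in the last 90 days, in conflict with the end-of-period status in the Primary outcomes text and in Table 3. It also leaves new starters with unequal time at risk if the window is fixed by calendar.

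Under a constant hazard with no return to care, the 20-point target is scored as 17.1 points, short of the stated 19. That shortfall is modest and depends on how the 19 was derived: under the intra-class correlation form of step 1, the requirement at a 59.3% control value is 15.4 to 17.0 points and 17.1 would just meet it. The hazards are taken from a Table 3 row about HIV-positive people, not ART patients. The false difference from starter mix is about 1 to 1.5 points at 50% retention, on the calendar reading only. Universal treatment could raise it, but the article gives no figure. Neither the net direction of error in the level nor the direction of bias between arms is established. The definition should be settled before the retention analysis.

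**What to change.** State the start of the 12 months: ART start, or window start for those already on ART. Include only patients whose 12 months plus 90 days fall within data capture. Score a default when a gap of more than 90 days begins inside the 12 months, using the 90 days beyond to see it. Use one clock (medication received, or coverage), one population and one statement of end-of-period status in Aim 3, Table 2, the Primary outcomes text and Table 3.

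Under the assumptions above, both groups would then score the true 50% and 70%.

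The cost is wording, programming and some patients. No new data collection is needed, because capture continues after the intervention closes. If capture ends on 31 December 2018, going back 90 days and then 365 days gives 2 October 2017, so patients starting ART after about early October 2017 are not in the final retention analysis. That is roughly the last ten months of starts in a 36-month intervention. Most of the 12 months of those starting later in that stretch would run past the July 2018 close in any case.
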